### Sample size

The estimated sample size required for this study is based on a previous study for chronic pain [40]. The calculator is freely available at https://glimmpse.samplesizeshop.org. To determine the sample size, we employed the Hotelling Lawley Trace statistical test with a power of 0.8 and an alpha error of 0.05 for pain assessment using the visual analogue scale. We accounted for two repeated measure dimensions, with the fixed predictor divided into two groups (active and sham), considering effects for group, time, and the interaction between group and time. The expected mean values per group for pain were 6.12 and 3.06 for the active group and 4.93 and 4.37 for the sham group, with a standard deviation of 3. Assuming constant variability across time (sphericity being 1), this analysis resulted in a total sample size of 94 participants. To account for anticipated attrition, we plan to recruit an additional ten participants, totaling 104 participants (active group, n = 52; sham group, n = 52).

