### Statistical analysis

Statistical analyses will be performed using SPSS software version 21.0 (IBM Corp., Armonk, NY, USA). All tabulated data will be analyzed by a blinded researcher through a sequence of randomized codes generated for data analysis. Clinical and sociodemographic characteristics will be described by means and standard deviations for continuous parameters and by frequency for dichotomous variables. By the end of the data collection, the blinded researcher and the researchers who evaluated the patients will check for double data entry and any other problem related to the data tabulation. The t-test and Qui-square test will analyze the continuous and dichotomous data for sociodemographic characteristics, respectively. The generalized estimating equations (GEE) or generalized mixed models will analyze the clinical data (primary and secondary outcomes: algometry, visual analogue scale, EHP-30, Facit-F) at baseline, final assessment (after 10 days of intervention), and follow-ups. According to the data analysis (residuals Q-Q plot, and histogram), we will choose the best distribution to represent the data. Also, we will decide to insert fixed or random factors to the constant based on A/C, B/C, and Q/C indexes, Chi-Square/DF, and the intraclass correlation coefficient. The link function will estimate the results according to the distribution of the dependent variable. Time, group (active and sham groups), and the interaction between them will represent the independent factors. The mean, mean difference, standard deviation, confidence interval, and p-value for baseline, final assessment, and follow-ups, will represent the data. It is important to mention that the PGI-C and sub-items from the BPI will be analyzed as continuous or dichotomic variables using regression analysis (linear or logistic) to explore the predictors of pain intensity and interference. The analysis will be conducted using generalized mixed models or Generalized Linear Mixed Models. We aim to verify the interaction between time and group, adjusting for confounders and modifiers effects if necessary. Also, the Wald x^2^ test will assess the significance of individual independent variables in the model. In contrast, the Bonferroni test will compare subgroups of independent variables [42]. Intention-to-treat analysis of missing data will be analyzed through follow-up data from those who do not complete the treatment protocol. If needed, we will perform imputation followed by sensitivity analysis, using the last value carried forward or group means. In the intention-to-treat analysis, we will select the most conservative value to avoid overestimating the results and confounding the analysis. For the sensitivity analysis, we will test the robustness of our results by analyzing all imputed datasets and describing any differences in the outcomes compared to the original analysis using generalized mixed models or generalized linear mixed models. If necessary, we may utilize the type III regression when dealing with unequal sample sizes and unbalanced designs that involve interactions between variables or missing data. This approach enables us to assess the unique contribution of each variable to the model’s prediction. Moreover, we will analyze and describe potential outliers based on the model’s residual plots. Additionally, sensitivity analyses may be performed to assess differences with and without the outliers. Effect sizes for interactions will be calculated for all outcomes using the partial η^2^ and mean difference. The significance level will be defined in all statistical testing as a p-value less than 0.05.

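### Missing data would be filled by last value carried forward or group means under an undefined most-conservative rule, which can understate standard errors or bias the treatment effect

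*Protocol article*

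**What the plan says.** All the relevant text is in the Statistical analysis section of the protocol article.

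- **Main model.** "The generalized estimating equations (GEE) or generalized mixed models will analyze the clinical data", with time, group and their interaction as factors. The choice between the two model families is left open.
- **Imputation.** "If needed, we will perform imputation followed by sensitivity analysis, using the last value carried forward or group means". The trigger is not stated. Nor is it stated which method applies to which outcome or visit, or whether a group mean is a mean of the visit value or of the change.
- **Selection rule.** "In the intention-to-treat analysis, we will select the most conservative value to avoid overestimating the results and confounding the analysis". Nothing says whether conservative is judged for each participant, for each arm or by the final result.
- **Robustness check.** "we will test the robustness of our results by analyzing all imputed datasets and describing any differences in the outcomes compared to the original analysis". This compares the imputed datasets with the main analysis, but names no method that varies the missing-data assumption in a controlled way.
- **Blinding of the analyst.** "All tabulated data will be analyzed by a blinded researcher through a sequence of randomized codes generated for data analysis".

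The only attrition figure is in the Sample size section: ten participants added to 94, giving 104 (52 per arm).

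**The concern.** Replacing a missing value by its arm mean adds a case that contributes to the sample size but not to the variance. Standard errors, confidence intervals and p-values all come out too small.

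Last value carried forward assumes that nothing changes after dropout. The plan itself expects change in both arms, so the method biases the estimate whenever dropout differs by arm. Unequal loss is plausible here: the Eligibility criteria section removes participants for headache after stimulation, which is a loss after treatment starts. The bias can also favour active stimulation. The Introduction reports that the gain in the one earlier endometriosis trial was sustained for one week, while follow-up here runs to two months. If benefit fades, carrying the post-treatment value forward overstates how long it lasts.

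The conservative rule is meant to guard against this but is not defined. What is at stake is the error rate and interval of the intention-to-treat comparison on every outcome, including the primary one, algometry.

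**Working it through.** **Inputs.** From the Sample size section: "Hotelling Lawley Trace statistical test with a power of 0.8 and an alpha error of 0.05" (two-sided assumed); means on the visual analogue scale of "6.12 and 3.06 for the active group and 4.93 and 4.37 for the sham group, with a standard deviation of 3"; N = 94, then 104. The within-person correlation is not stated. Simulations used 0.5, two time points and random dropout, all assumed. The 10-of-52 and unequal dropout rates are also assumed.

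**The plan's own figure.** Difference in change = (6.12 − 3.06) − (4.93 − 4.37) = 2.50. With zero correlation, the SD of change is 3√2 = 4.24. The normal formula gives a total of 92 and the t-based one gives 94 (power 0.807), so the stated 94 reproduces. The attrition allowance is 10/104 = 9.6%, about 5 of 52 per arm.

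**Group means, single visit.** With m observed of n per arm, naive SE / true SE = √[m(m−1) / (n(n−1))].
- m = 47, n = 52: √(47×46 / (52×51)) = 0.903. Then 2[1 − Φ(1.96 × 0.903)] = 7.7%. Simulation: 7.7%.
- m = 42, n = 52: ratio 0.806, giving 11.4%. Simulation: 11.3%.
- With the abstract's 20 per arm and 18 observed: ratio 0.897, giving 7.8% to 7.9%.

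**Group means, planned group-by-time test.** The baseline is observed for everyone, and only the later visit is filled with its arm mean.
- True variance of an arm's mean change: σ²(1/m + 1/n − 2ρ/n) = σ²(n + m − 2ρm)/(mn).
- Apparent variance, approximately: σ²[2(1−ρ)m + (n−m)]/n² = σ²(n + m − 2ρm)/n².
- The SE ratio is therefore √(m/n), whatever the correlation.
- m = 47: √(47/52) = 0.951, giving 6.2%. Simulation: about 6.3%.
- m = 42: √(42/52) = 0.899, giving 7.8%. Simulation: about 8%.

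If the arm mean of the change were imputed instead, the single-visit ratio would apply to this test too (simulated 7.7% and 11.7%). The plan does not say which is meant.

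These ratios are free of scale, so they hold for algometry as well.

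**Last value carried forward, no true difference.** Bias = drift × (dropout in active − dropout in sham).
- 1.5 × (0.15 − 0.05) = 0.15 points against active.
- 3.06 × 10/52 = 0.59 points when only one arm loses participants, with type I error of about 16% to 17%. The sign reverses with the arm.
- Equal random dropout and no drift: type I error near 5%.

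**Last value carried forward, planned effect of 2.50.**
- 5 missing in each arm: 2.50 × 47/52 = 2.26.
- 10 missing in active only: 3.06 × 42/52 − 0.56 = 1.91.
- 10 missing in sham only: 3.06 − 0.56 × 42/52 = 2.61, an overstatement.

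**The conservative rule.**
- Larger of the two p-values: about 5% or lower (4.2% in the one-arm dropout example).
- Smaller of the two: about 20% in that same example.
- Worse value for each participant: about 6% with 8 versus 3 missing and a 1.5-point drift. When only sham loses participants, the worse value is never better than the carried-forward one, so the effect is overstated at least as much as the 2.61 above.

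**No imputation.** Analysing the observed data only, simulated type I error was 5.1% to 5.2%, and the planned effect was recovered as 2.50.

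**The case against.** The strongest reply has five parts.

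- **Imputation is conditional, and the un-imputed analysis is reported beside it.** True. It lowers the chance that the flaw decides the result, but the intention-to-treat rule still stands as written.
- **The rule concerns a value, not a result.** A reader might infer that the plan lets the team choose among results once they are seen. The text does not say so: "we will select the most conservative value to avoid overestimating the results and confounding the analysis" more naturally describes which imputed number to enter. The defect is that the rule is undefined.
- **Conservative choices protect the error rate.** This holds if the larger p-value is meant. It does not always hold if the worse value for each participant is meant. Even the larger p-value leaves a biased estimate and interval.
- **The analyst is blinded.** Coded data reduce the freedom to choose the method and value but do not remove it, because the data are still in view when the choice is made.
- **The sizes rest on assumptions.** Only the 9.6% allowance is the plan's own. The 0.15-point bias is 6% of the planned 2.50 difference and runs against active, on a secondary outcome. No bias has been quantified for algometry, for which the article gives no means.

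It is also fair to say that a repeated-measures model copes with incomplete participants under missing-at-random only if the mixed model is chosen. Ordinary GEE needs a stronger assumption.

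**Conclusion.** The concern holds in a limited form. The plan names two weak single-imputation methods and an undefined rule for choosing between values, and nothing else in the section repairs this. It should be changed, but it does not by itself invalidate the trial.

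At the plan's attrition allowance, group means used alone raise the type I error to about 6.3% for the planned group-by-time test, if visit values are imputed. The 7.7% and 11.5% figures describe a single-visit comparison, and a reader should not carry them over to the planned test without knowing which mean is imputed. It would also be wrong to say that both methods understate the standard error: that charge fits group means. For last value carried forward the problem is bias of unpredictable sign, which needs both drift and unequal dropout; the 0.15 and 0.59 point examples assume both.

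That the stated rules can mislead is certain. The size in this trial is uncertain, because it depends on dropout that has not been observed.

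**What to change.** 1. Name the likelihood-based mixed model on all observed visits, with no imputation, as the primary intention-to-treat analysis, and state the missing-at-random assumption. Do not leave ordinary GEE as an equal alternative for this purpose.
2. Delete last value carried forward, group means and the most-conservative-value rule.
3. For sensitivity, use multiple imputation by arm with baseline and earlier visits as predictors, combined by Rubin's rules, plus a delta-adjusted version in which outcomes after dropout are made worse by stated amounts.

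The cost is a change of wording and a little extra analysis. The stated sample size of 94, or 104 with attrition, is not affected.

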
### Data monitoring

This study will not involve participants at risk of death or interventions that are harmful; therefore, it will not be necessary to create a data safety monitoring board. In case of severe adverse events that demand an interruption of the trial, the principal investigator will perform the interim analysis and will inform the ethics committee and The Brazilian Registry of Clinical Trials. The principal investigator will decide on the viability of publishing the data.

### Harms

Any adverse events will be carefully monitored in all steps of the study by asking patients, after each session of stimulation and during the follow-up periods, if they experienced any unusual symptoms or adverse events, and their perception of the relationship between these events and the treatment they received with tDCS. Any adverse event during the research period will be registered and considered in the data analysis. We will interrupt the interventions if any risk to the patients is suspected. Adverse events might include pain, fatigue, itching, tingling, headache, burning, discomfort, dizziness, and cardiovascular symptoms, such as shortness of breath, chest pain, and abnormally increased blood pressure. Although some adverse events can be observed, real-world improvements in pain, quality of life, and fatigue are expected. Although the participants are exposed to certain adverse events, the improvements particularly related to pain seem to be promising.

### Ethics and dissemination

This project was submitted to the Research Ethics Committee of the Federal University of Rio Grande do Norte and approved under protocol number 5.635.439. All participants will be informed about the research protocol and, if agree, they will sign the written informed consent before beginning any aspect of the study protocol. The study will be conducted following the principles of the Declaration of Helsinki and was registered on the virtual platform Brazilian Clinical Trials Registry (RBR-4q69573). Any personal information related to participation in the research will not be shared during or after the study. All participants will be informed about the trial’s objectives and procedures and that they will participate voluntarily, as determined by Resolution No. 466/12 of the National Health Council. After the study, all patients who received the sham tDCS will be invited to receive the active tDCS, which will be provided to them at no cost.
